## Abstract

Seasonal influenza has a significant annual global impact. Current influenza vaccines work by inducing strain-specific antibodies against the highly polymorphic surface proteins of the influenza virus and need to be redesigned every year, increasing their cost and limiting availability. There is a demand for a more efficacious vaccine, particularly in older adults in which the current vaccines show poor efficacy. The aim is to investigate a novel vaccine, MVA-NP+M1, which targets T cell responses to the nucleoprotein and matrix 1 core proteins of the influenza virus A, which are highly conserved,
**  **and therefore may provide long protection against a broad range of influenza strains.

INVICTUS is a phase IIb study to determine the safety and efficacy of candidate
INfluenza
Vaccine MVA-NP+M1 in combination with licensed
Ina
CTivated infl
Uenza vaccine in adult
S aged 65 years and above is a randomised, participant-blinded, placebo-controlled, multi-centre phase IIb efficacy study planned for 2030 volunteers aged 65 and over, in primary care. The primary objective is to assess the efficacy of MVA-NP+M1 co-administered with licensed inactivated quadrivalent influenza vaccine in adults ≥65 years. Participants complete daily diaries to record solicited and unsolicited events in the first four weeks post vaccination, and influenza-like illness (ILI) symptoms and severity throughout the influenza season.

We hypothesise an improvement in the primary outcome, a reduction in the average number of days spent with moderate or severe influenza-like illness during periods of influenza circulation, in the group administered with MVA-NP+M1, compared to those in the control group.

**Registration: **ClinicalTrials.gov identifier
NCT03300362.

**Protocol version:** INVICTUS Protocol v3.0, 08 June06 2018.

## Abbreviations

AE, adverse event; CI, chief investigator; CRF, case report form; DMEC, data monitoring ethics committee; GCP, good clinical practice; GP, general practitioner; ICH, International Conference on Harmonisation; MHRA, Medicines and Healthcare products Regulatory Agency; MVA, modified vaccinia virus Ankara; NP, nucleoprotein; Pfu, plaque forming units; PIS, participant information sheet; QA, quality assurance; REC, research ethics committee; SAE, serious adverse event; SMPC, summary of medicinal product characteristics; SUSAR, suspected unexpected serious adverse reactions.

## Introduction

Seasonal influenza has a significant annual global impact accounting for an estimated 1 billion illnesses and 250,000–500,000 deaths
^1^ with an estimated economic cost of $87.1 billion in the US alone
^2^. The unpredictable risk of sporadic outbreaks of human infections with avian influenza (H5N1) could trigger a new pandemic if the virus acquires the ability to transmit from person to person
^3^. 

Vaccination remains the most cost-effective strategy available to combat influenza. Current influenza vaccines work by inducing strain-specific antibodies against the highly polymorphic surface proteins (haemagglutinin, neuraminidase) of the influenza virus. Vaccines are produced based on a prediction of strains likely to circulate in the population in the upcoming influenza season. The need for constant redesign and remanufacture increases cost and places limitations on vaccine supply
^4^, potentially leaving large populations susceptible to infection and illness. Efficacy of currently available influenza vaccines is significantly reduced in older adults (30–40%) compared to younger groups (70–90%)
^5^, which highlights the need for better protection in this age group.

When individuals are exposed to new influenza virus strains, to which they lack protective neutralising antibodies, cross-reactive T-cells against conserved internal antigens of influenza are associated with less viral shedding, reduced symptoms duration and severity
^6,
7^. We constructed MVA-NP+M1, a recombinant, replication-deficient modified vaccinia Ankara (MVA) vector expressing the conserved influenza antigens nucleoprotein (NP) and matrix 1 (M1) as a fusion protein
^8^, in the novel immortalised duck retinal cell line AGE1.CR.pIX. The aim of the vaccine is to boost cross-reactive T-cell responses to protective levels, providing immunity to not only human seasonal influenza, but also other influenza A subtypes currently found in avian species or swine.

Prior to INVICTUS, MVA-NP+M1 has been administered to 151 adults in seven clinical trials (see
Table 1). The vaccine generally boosted T-cell responses when administered to healthy adults. In a small, un-randomised Phase IIa challenge study, fewer vaccinated volunteers developed influenza than unvaccinated ones and there was a trend toward a reduction in duration of virus shedding in vaccinated volunteers
^9^. The vaccine has been shown to have a good safety profile with no vaccine related serious adverse events (SAE) in these trials.

**Table 1. T1:** Clinical studies to date using MVA-NP+M1 (Total n=151).

Country	Study	Vaccine	Age	Route	Dose of MVA- NP+M1	Number of volunteers
UK	FLU001	MVA-NP+M1	18–50	ID	5 ×10 ^7^ pfu	12
		MVA-NP+M1	18–50	IM	5 ×10 ^7^ pfu	8
		MVA-NP+M1	18–50	IM	2.5 ×10 ^8^ pfu	8
		MVA-NP+M1	50–59	IM	1.5 ×10 ^8^ pfu	10
		MVA-NP+M1	60–69	IM	1.5 ×10 ^8^ pfu	10
		MVA-NP+M1	70+	IM	1.5 ×10 ^8^ pfu	10
UK	FLU002	MVA-NP+M1	18–50	IM	1.5 ×10 ^8^ pfu	15
UK	FLU003	MVA-NP+M1 (together with seasonal influenza vaccine)	50+	IM	1.5 ×10 ^8^ pfu	9
UK	FLU004	ChAdOx1-NP+M1/MVA-NP+M1 ( *7–14 weeks apart*)	18–50	IM	1.5 ×10 ^8^ pfu	3
UK	FLU005	ChAdOx1-NP+M1 / MVA-NP+M1 *(8 weeks apart)*	18–50	IM	1.5 ×10 ^8^ pfu	12
		ChAdOx1-NP+M1 / MVA-NP+M1 *(52 weeks apart)*	18–50	IM	1.5 ×10 ^8^ pfu	8
		MVA-NP+M1 / ChAdOx1-NP+M1 *(8 weeks apart)*	18–50	IM	1.5 ×10 ^8^ pfu	13
		ChAdOx1-NP+M1 / MVA-NP+M1 *(52 weeks apart)*	18–50	IM	1.5 ×10 ^8^ pfu	12
		ChAdOx1-NP+M1 / MVA-NP+M1 *(8 weeks apart)*	>50+	IM	1.5 ×10 ^8^ pfu	12
UK	FLU006	MVA-NP+M1 ( *co-administered with seasonal* *influenza vaccine - Viroflu®*	>50	IM	1.5 ×10 ^8^ pfu	3
UK	FLU008	MVA-NP+M1 *(AGE1.CR.pIX cell line)*	18–50	IM	1.5 ×10 ^8^ pfu	6

## Protocol

### Methods and design

***Ethics and dissemination*.** The trial is conducted according to the principles of the Declaration of Helsinki, relevant regulations and good clinical practice, and will be disseminated through publication in peer-reviewed scientific journals. The study was approved by the South Central, Berkshire Research Ethics Committee (17/SC/0300).

### Objectives

The primary objective is to assess the efficacy of MVA-NP+M1 in combination with licensed inactivated influenza vaccine (IIV) in adults ≥65 years. See
Table 3 for details of all objectives.

**Table 3. T3:** Objectives, outcome measures and time-points.

Objectives	Outcome Measures	Timepoint(s) of evaluation and data collection method for this outcome measure (if applicable)
**Primary Objective** To assess the efficacy of MVA-NP+M1 in combination with licensed inactivated influenza vaccine in adults ≥65 years.	**Primary endpoint:** 1. Number of days with moderate or severe influenza-like symptoms	Throughout the influenza season - Self-reported symptoms recorded using electronic or paper diaries
**Secondary Objectives** To assess the incidence of ILI in adults aged 65 years and above vaccinated with MVA-NP+M1 or Placebo in combination with the recommended annual licensed inactivated vaccine.	1. Incidence of influenza-like-illness	Throughout the influenza season - Self-reported symptoms recorded using electronic or paper diaries
To assess the severity of influenza-like symptoms in adults aged 65 years and above vaccinated with MVA-NP+M1 or Placebo in combination with the recommended annual licensed inactivated vaccine	2. Severity of influenza-like symptoms	Throughout the influenza season - Self-reported symptoms recorded using electronic or paper diaries
To assess the duration of ILI in adults aged 65 years and above vaccinated with MVA-NP+M1 or Placebo in combination with the recommended annual licensed inactivated vaccine	3. Duration of influenza-like-illness	Throughout the influenza season - Self-reported symptoms will be recorded using electronic or paper diaries
To assess the occurrence of GP consultations from respiratory illness in adults aged 65 years and above vaccinated with MVA-NP+M1 or Placebo in combination with the recommended annual licensed inactivated vaccine	4. Occurrence of GP consultations from respiratory illness	Throughout the influenza season - Self-reported and Medical Records
To assess the hospitalisations and deaths due to respiratory illness in adults aged 65 years and above vaccinated with MVA-NP+M1 or Placebo in combination with the recommended annual licensed inactivated vaccine	5. Occurrence of hospitalisations and deaths due to respiratory illness	Throughout the influenza season - Self-reported and Medical Records
To assess the safety and reactogenicity of MVA-NP+M1 in combination with licensed inactivated influenza vaccine in adults ≥65 years. To assess the immunogenicity of MVA-NP+M1 or Placebo in combination with the recommended licensed inactivated influenza vaccine in adults aged 65 years and above To assess the presence of the influenza virus using virological markers, in adults aged 65 years and above vaccinated with MVA- NP+M1 or Placebo in combination with the recommended annual licensed inactivated vaccine	6. Occurrence of solicited local and systemic reactogenicity signs and symptoms for 7 days following vaccination 7. Occurrence of unsolicited adverse events for 28 days following vaccination 8. Occurrence of serious adverse events throughout participants’ participation in the trial - Frequency of influenza-specific T-cells measured by IFN-γ ELISpot - Geometric mean titre of influenza-specific neutralising antibodies - Breadth of influenza-specific T-cells and antibodies 1. Incidence rate of laboratory confirmed influenza using RT-PCR.	Day 0–7 - Self-reported symptoms recorded using electronic or paper diaries Day 0–28 - Self-reported symptoms recorded using electronic or paper diaries Telephone calls on Day 1–3, day 7–9 and every 3–4 weeks throughout participants’ participation in the trial Blood samples drawn at enrolment (before vaccinations), day 21 and at the end of the influenza season Nasal swab sample taken by participant at the time of self-reported symptoms. Nasal swabs will be taken during the first 3 days of the onset of the self-reported symptoms
**Tertiary Objectives** To explore novel clinical endpoints for future Phase III efficacy trials of influenza vaccines	1. Estimated frequency of influenza infection using historical data on the proportion of ILIs that is caused by influenza virus infection.	At the end of the influenza season

### Study design

The trial is an individually randomised, participant-blinded, placebo-controlled, multi-centre phase IIb efficacy study in 2030 volunteers aged 65 and over, in England. The main study is set in primary care and a separate immunology sub-cohort of 100 participants will be recruited at the Jenner Institute, University of Oxford. The trial will be promoted through various media sources.

### Interventions

Participants are randomly assigned to either the control (licensed IIV and placebo) or intervention group (licensed IIV and MVA-NP+M1) by the Research Nurse.

***MVA-NP+M1*.** The vaccine has been described previously and consists of a replication deficient MVA viral vector expressing the NP and M1 antigens from the influenza A virus (H3N2, 87 A/Panama/2007/99) as a single fusion protein
^8^. A dose of 1.5 ×10
^8^ pfu will be used. MVA-NP+M1 is manufactured under good manufacturing practice conditions by Emergent Biosolutions, USA, and is certified and labelled for trial at the Clinical Biomanufacturing Facility, University of Oxford. The vaccine is stored at -80°C in a temperature monitored, secure freezer at the clinical sites.

***Seasonal influenza vaccine (licensed IIV)*.** Pre-packaged needle and syringe containing 0.5 ml licensed IIV (Split Virion) is stored at 2°C to 8°C in a secure, temperature-monitored refrigerator at site. 

***Placebo*.** Participants allocated to the control group will receive an intramuscular injection of 0.9% saline. The volume and site of injection will be the same as for the MVA-NP+M1 group.

### Trial procedures

***Informed consent*.** Once eligibility has been confirmed (
Table 2), participants provide written informed consent before any study procedures are performed. The participant is fully informed of all aspects of the trial, the potential risks and their obligations, and will be able to ask questions.

**Table 2. T2:** Eligibility criteria.

Inclusion Criteria	Exclusion Criteria
• Volunteer is willing and has capacity to provide written informed consent for participation in the trial (in the Investigator’s opinion). • Male or female adults, aged 65 years and above • Able and willing (in the Investigator’s opinion) to comply with all study requirements • Willing to allow the investigators to discuss the volunteer’s medical history with their General Practitioner • Eligible to receive seasonal influenza vaccine	• Any history of anaphylaxis in reaction to vaccination or history of allergic reactions likely to be exacerbated by any component of the vaccine (e.g. egg allergy) • Ongoing terminal illness with a life expectancy estimated to be approximately <6 months. • Continuous use of oral anticoagulants, such as coumarins and related anticoagulants (i.e. warfarin) or novel oral anticoagulants (i.e. apixaban, rivaroxaban, dabigatran and edoxaban) • Any other significant disease, disorder or finding (including blood test results), which, in the opinion of the Investigators, would either put the volunteer at risk because of participation in the study, or may influence the result of the study • Participation in another clinical trial of an investigational medicinal product in the 30 days preceding enrolment, or planned use during the study period • Prior receipt of an investigational vaccine likely to impact on interpretation of the trial data • Receipt of annual seasonal influenza vaccine prior to enrolment (for the same influenza season volunteers are recruited in) • Not willing to comply with study procedures

***Vaccination procedure*.** The seasonal influenza vaccine is administered first, and then saline or MVA-NP+M1 administered no longer than 5 minutes after, within a 1cm circle. All vaccines are administered intramuscularly into the deltoid region of the arm. 

***Participant observation*.** Participants are observed for a minimum of 10 minutes after vaccination. Medicines and resuscitation equipment are available for the management of anaphylaxis. Participants are provided with an oral thermometer, follow-up diaries and a card with study contact details. An out of hours telephone number is provided.

***Vaccination postponement*.** Vaccination may be postponed in any of the following events at the time of vaccination.

 Acute disease Temperature of >37.5°C. Receipt of a licensed inactivated vaccine within 2 weeks prior to enrolment. Receipt of a licensed live vaccine within 4 weeks prior to enrolment.

### Sub-cohort

A sub-cohort of participants (50 for each of two seasons) will be recruited to assess the immunogenicity of MVA-NP+M1 in combination with the licensed IIV. In addition to the procedures described for the main cohort, the sub-cohort attend a screening visit, and three further visits where blood samples are taken for monitoring of laboratory AEs and immunology purposes at weeks 1, 3 and 26. Blood samples will be stored in compliance with the Human Tissue Act (2004).

### Follow-Up procedures

***Participant Diaries*.** Participants record their symptoms in electronic diaries or paper diaries. Daily or weekly reminders are sent.

**Week 1 diary**. Participants are asked to record the occurrence and severity of solicited and unsolicited adverse events for one week. The following solicited adverse events are recorded by participants: local (pain, redness, warmth and pruritus at injection site) and systemic (feverishness, chills, myalgia, fatigue, headache, nausea, vomiting, arthralgia, malaise and oral temperature). 

**Week 2–4 diary**. From weeks 2–4, participants report unsolicited adverse events, and influenza-like illness (ILI): feverishness, cough, sore throat, malaise, headache, myalgia, shortness of breath, runny/blocked nose, sneezing and temperature. For the duration of ILI symptoms they record: the severity of symptoms (mild, moderate or severe), oral temperature and any new medication.

**Daily and symptom diary**. From week 5 until the end of the flu season, participants are only required to report ILI as described for weeks 2–4.

***Safety follow-up*.** Participants are contacted at 24 (+48 h) hours, on day 7 (+2 days) and every 3–4 weeks after vaccination, to monitor and record the occurrence of any SAEs and GP consultations, remind participants to complete their diary and to collect ILI data when a diary hasn’t been completed.

### Medical notes review

A medical notes review is conducted to collect details of any occurrences in the follow-up period of: laboratory-diagnosed influenza illness, medically attended respiratory illness, GP consultations, antibiotic prescriptions and hospitalisations.

### Data management

Details can be found in the Data Management Plan, held at the PC-CTU, University of Oxford. The plan is also available as
*Extended data*
^10^.

***Confidentiality*.** Participants will be identified only by a participant ID number. The trial will comply with the Data Protection Act 2018. All documents will be stored securely and only accessible by trial staff and authorised personnel, at the University of Oxford.

***Access to data*.** Vaccitech Ltd. and the University of Oxford will have access to the final trial dataset. GP sites will have access to the dataset for participants registered at their practice. Access to the data will be outlined in the relevant contract.

### Outcomes

***Primary endpoint*.** The primary endpoint is the number of days with moderate or severe ILI during the influenza season defined using UK surveillance data. A protocol ILI definition will be adopted for the purposes of analysis: feeling feverish or having a fever (temperature ≥37.8°C) and at least one of the following symptoms: a cough and/or sore throat. See
Table 3. for details of all primary, secondary and tertiary endpoints.

### Randomisation

The study team obtain the randomised group allocation through a validated and secured web-based server (Sortition®). Randomisation will use non-deterministic minimisation on practice, age and gender to ensure each arm is balanced and 1:1 allocation when all participants have been recruited. The immunology sub-cohort will be randomised separately using the same method. Emergency randomisation procedure is also available if the web-based system isn’t accessible.

### Blinding

The participant is blinded to the group they have been allocated to, but the staff administering the vaccine aren’t blinded. Investigators recording and assessing clinical and safety outcomes are blinded to group allocation.

### Sample size

We assumed the average number of days spent with moderate or severe ILI per “season” of circulation was 3.5 days and a typical follow-up period for a season of approximately 120 days across this corresponds to 2.92% of days [6]. A sample size of 2,030 (1,015 per group) will provide 85% power to detect a relative drop of 20% in the primary outcome between the two groups (from 2.92% to 2.34%) at 5% level of significance (2-sided). This sample size has accounted for a 25% attrition rate and a further 15% increase to account for clustering of participants within households, which are estimated to be 0.04.

For the secondary outcomes, we estimated that 12.25% of vaccinated individuals over 65 years old experience an ILI most likely attributable to influenza [6].The proposed sample size will have 90% power to a reduction in the percentage of individuals experiencing ILI from 28.5–22.25%. We estimate a 50% improvement in vaccine efficacy over the IIV alone in reducing the occurrence of ILI due to influenza during periods of influenza circulation.

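### The stated 85% power for the primary outcome conflicts with the same section's 28.5% ILI incidence and 3.5 mean days; on those inputs it is about 63–72% or lower

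*Protocol article*

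**What the plan says.** All the figures are in the Sample size section of the protocol article unless noted.

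- Control rate: "average number of days spent with moderate or severe ILI per “season” of circulation was 3.5 days". Spread over some 120 days of observation, the plan puts this at 2.92%.
- Effect and test: the daily rate moves "from 2.92% to 2.34"%, tested "at 5% level of significance (2-sided"). Allocation is "1:1 allocation when all participants have been recruited" (Randomisation).
- Claim: "A sample size of 2,030 (1,015 per group) will provide 85% power to detect a relative drop of 20% in the primary outcome".
- Allowances: "This sample size has accounted for a 25% attrition rate". Another 15% is added for household clustering, to which the value 0.04 is attached.
- Secondary outcome, next paragraph: "a reduction in the percentage of individuals experiencing ILI from 28.5–22.25"%.

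The Outcomes section defines the primary endpoint as days with moderate or severe ILI, under a protocol ILI definition. The Statistics section counts symptom days only in participants who meet that definition. It fits a mixed-effects logistic model with random effects for household and for days within participant. The sample-size text gives no separate value for the correlation of days within a participant.

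**The concern.** Days of illness bunch within the people who fall ill, so the variance of days per participant depends heavily on how many people fall ill at all. If only 28.5% contribute any days, yet the mean over everyone is 3.5, the ill must average 3.5 / 0.285 = 12.3 days and the other 71.5% sit at zero. That sets a floor under the variance whatever the distribution of illness lengths. The question is whether the variance needed for 85% power lies above that floor. If it does not, the chance of missing a true 20% reduction exceeds the stated 15%, and a null primary result would carry less evidence against the vaccine than the protocol implies.

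**Working it through.** **1. Reproduce the stated figure.** Control rate p1 = 3.5/120 = 0.02917. Intervention rate p2 = 2.8/120 = 0.02333. Two-sided alpha is 0.05 and power 0.85, so (1.960 + 1.036)² = 8.978.

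- Independent person-days per arm: 8.978 × [p1(1−p1) + p2(1−p2)] / (p1−p2)² ≈ 13,484.
- Design effect, taking 0.04 as the correlation of days within a participant: 1 + 119 × 0.04 = 5.76.
- Participants per arm: 13,484 × 5.76 / 120 ≈ 647.
- Inflation: 647.2 / 0.85 / 0.75 = 1,015, the stated figure. With ×1.15 in place of /0.85 it is 992. Rounded rates and a continuity correction move the total N between 1,985 and 2,062.

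So 85% does reproduce, but only with 0.04 in that role. With no clustering of days, power would be about 100%. Nor does 0.04 explain the 15% household increase: 1 + (m−1) × 0.04 = 1.15 needs m = 4.75 participants per household.

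**2. What that input implies.** Variance of days per control participant = 120 × p1(1−p1) × 5.76 = 19.6, so SD = 4.42. For a non-negative count with mean μ and a share p non-zero, Var ≥ μ²(1/p − 1). Solving for p with μ = 3.5 and Var = 19.6 gives p ≥ 12.25 / (19.57 + 12.25) = 38.5%.

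**3. What 28.5% implies.** Var ≥ 3.5² × (1/0.285 − 1) = 30.7, so SD ≥ 5.54. Equality needs every ill participant to have exactly 12.3 days. The matching correlation of days is at least [30.73 / (120 × 0.02917 × 0.97083) − 1] / 119 = 0.068.

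**4. What 85% needs.** Effective size per arm with the plan's allowances: 1,015 × 0.75 / 1.15 = 662. For a difference of 0.7 day, SD = 0.7 / (2.996 × √(2/662)) = 4.25 with equal variances. This is below the floor of 5.54.

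**5. Power on the plan's inputs.** Power = Φ(0.7 / √((V_c + V_t)/662) − 1.96), for a comparison of mean days. V_c and V_t are the control and intervention variances. With equal illness lengths V_c = 30.73.

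| Scenario | V_t (equal lengths) | Power, equal lengths | Power, CV of days per case 0.5 (assumed) |
|---|---|---|---|
| Control variance used in both arms | 30.73 | 63% | 51% |
| Incidence falls to 22.25%, mean 2.8 | 27.40 | 66% | 53% |
| Duration only, incidence stays 28.5% | 19.67 | 72% | 59% |

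Using /0.85 instead of /1.15 (647 per arm) lowers each entry by about one point. Dropping the household allowance (761 per arm) gives 69%, 72% and 78% with equal lengths.

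**6. Planned type of model.** Small simulations of a logistic model with a participant random intercept, at 662 per arm, gave roughly 54–68%. They covered incidence-driven effects at CV 0.5 and 1.0 and a duration-driven effect at CV 1.0. They used 200 to 400 trials per scenario (Monte Carlo standard error about 2.4 to 3.5 points), and no covariate adjustment is reported.

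**7. Drop detectable at 85% power.** Mean days, equal lengths, incidence-driven: a 25% drop gives V_t = 0.21375 × 0.78625 × 12.28² = 25.3. The detectable difference is then 2.996 × √((30.7 + 25.3)/662) = 0.87 day, and 0.87/3.5 = 25%. Using the control variance in both arms it is 26%.

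**The case against.** **The analysis is not a comparison of means.** This stands as a limit on precision. The planned mixed logistic model responds differently when illness lengths vary. A reader might infer from a two-means calculation at a CV of 1.0 that power falls to about a third (32–37%). The documents do not support that for this trial, because simulations of the planned type of model at that CV gave about 55–68%. None of these reached 85% either.

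**The effect might come through duration.** The Introduction links cross-reactive T cells to shorter and milder illness, so this is plausible. It raises the figure to about 72% with equal illness lengths. A reader might infer that two-thirds is a ceiling; it is not. Exceeding 85% at the plan's incidence takes a duration-only effect, identical illness lengths and all 1,015 per arm with no losses (88%). The plan itself assumes losses and a fall in incidence.

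**0.04 is attached to households.** Correct. Its use as a within-participant correlation is an inference from arithmetic that fits closely. The bound in steps 3 and 4 does not depend on it.

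**The 28.5% and the 3.5 days may not share a definition.** Table 3 words the primary endpoint as influenza-like symptoms, which could give more participants non-zero days. At 40% non-zero, falling to 32% with equal lengths, power at 662 per arm would be 86%. But Outcomes and Statistics both tie the endpoint to the protocol ILI definition, and the source cited for 3.5 days cannot be checked here. If the definitions do differ, the section should say so.

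**Confidence intervals will be reported.** They would show the imprecision of a null result, which softens the consequence. The stated power remains wrong.

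**Conclusion.** The point holds as an internal contradiction. Under the ILI endpoint, 3.5 mean days and 28.5% incidence force an SD of at least 5.54 days, and 85% power after the plan's allowances needs about 4.25. That part is algebra and assumes no distribution.

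The size of the shortfall is less certain. For mean days with equal illness lengths, power is about 63–66% if the effect comes through incidence and about 72% if only through duration. At an assumed CV of 0.5 it is about 51–59%. The model simulations gave roughly 54–68%. These figures take the 25% attrition and the 15% household increase as full losses, as the plan does, and ignore any gain from covariates.

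A reader might conclude that 85% cannot be derived at all. It can, but only from an input that contradicts the 28.5%. Nor does the point show bias, an inflated type I error or a safety problem.

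**What to change.** In the Sample size section:

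1. Reconcile 3.5 days, 28.5% and 0.04. If 28.5% and 3.5 days use different definitions or periods, state them, and align the wording in Table 3 with Outcomes.
2. State which clustering 0.04 describes, and give the correlation of days within a participant that was used.
3. Restate the power for a 20% drop under the planned mixed logistic model, with inputs consistent with 28.5% incidence. On present evidence this is about 65–70% or lower. Show a range for the spread of illness length and for incidence-driven versus duration-driven effects.
4. State the drop detectable at 85% power: at least about 25% for mean days with equal illness lengths and an incidence-driven effect.

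The cost is a modest simulation and a rewritten paragraph. Enrolment need not change; the only downside is a less favourable stated power.

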### Statistics

***Description of statistical methods*.** The primary statistical analysis will be by intention-to-treat (ITT). Between group comparisons will be presented using effect measures (ratio or difference in response rate, difference in means) with 95% confidence intervals.

The primary outcome will be modelled using a generalised linear mixed effect logistic model, adjusting for flu season (first or second season), age, sex, GP practice and chronic illnesses. The outcome will be presence of any of the listed symptoms (feverishness, cough, sore throat, malaise, headache, myalgia, shortness of breath and temperature) rated as moderate or severe by participants who meet the protocol ILI definition on any of the days that are included for study purposes. Random effects will be incorporated to account for the clustering of participants within households and to account for the clustering of data over days within participant.

Comparison between groups of the proportion of participants experiencing an ILI will be carried out using the same method as the. The mixed effects will acknowledge the clustering of participants within households. The effect measure presented for MVA-NP+M1 compared to IIV alone will be an adjusted odds ratio with 95% confidence interval, which can be interpreted as an adjusted relative risk given the low prevalence.

We will use mixed-effect model, or an equivalent nonparametric method where appropriate, to analyse continuous secondary outcomes, adjusting for the same baseline measures and stratification variables. We will compare the safety outcomes using Chi-squared or Fisher’s exact test.

All the tests will be done at a 5% two-sided significance level. Data analysis will be restricted to the periods where acute respiratory illnesses are likely to be attributable to influenza based on local and national surveillance intelligence.

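### The 90% power stated for ILI incidence holds only if all 1,015 enrolled per arm are analysed as independent; on the protocol's own allowances it is about 75% to 80%

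*Protocol article*

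**What the plan says.** All the figures are in the Sample size section of the protocol article. For the primary outcome: "A sample size of 2,030 (1,015 per group) will provide 85% power to detect a relative drop of 20% in the primary outcome". On what that number contains: "This sample size has accounted for a 25% attrition rate and a further 15% increase to account for clustering of participants within households". The clustering is put at 0.04, without saying what kind of quantity this is.

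The next paragraph turns to the secondary outcomes. It states that "we estimated that 12.25% of vaccinated individuals over 65 years old experience an ILI most likely attributable to influenza", and then: "The proposed sample size will have 90% power to a reduction in the percentage of individuals experiencing ILI from 28.5–22.25" (per cent). It adds an expected 50% improvement in vaccine efficacy over the licensed vaccine alone. It gives no separate attrition or clustering assumption for this outcome.

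The Statistics section sets the error rate: "All the tests will be done at a 5% two-sided significance level". For the comparison of the proportion of participants with ILI it says: "The mixed effects will acknowledge the clustering of participants within households". Table 3 lists ILI incidence as the first secondary outcome and collects it through the same self-reported diaries as the primary endpoint.

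**The concern.** A number that has been inflated for dropout and clustering should not be used uninflated for a second power claim. If 1,015 per arm is the gross enrolment, fewer are expected to be evaluable, and those who share a household may carry less information than the same number of unrelated people. Both allowances look relevant to ILI incidence: its data come from the same diaries as the primary endpoint, and its planned model accounts for households.

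What is at stake is how a null result would be read. ILI incidence is the only secondary outcome for which the article gives a power figure. A non-significant result in a comparison believed to have 90% power counts more heavily against an effect than one with 75% to 80%.

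**Working it through.** **Inputs.** From Sample size: p1 = 0.285, p2 = 0.2225, n = 1,015 per arm, 25% attrition, 15% for clustering. From Statistics: two-sided α = 0.05, so z = 1.960. From Randomisation: 1:1 allocation. The check uses a two-proportion normal approximation with unpooled variance in place of the planned mixed logistic model.

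**Formulae.**
- Difference: d = 0.285 − 0.2225 = 0.0625
- Variance sum: V = 0.285 × 0.715 + 0.2225 × 0.7775 = 0.37677
- Power = Φ(d / √(V/n) − 1.960)
- n per arm for 90% power = (1.960 + 1.2816)² × V / d²

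**Reproducing the stated 90%.**
- Required n = 10.508 × 0.37677 / 0.00390625 ≈ 1,013.5 per arm, which is almost exactly the enrolment.
- At n = 1,015: √(0.37677/1,015) = 0.01927; 0.0625/0.01927 = 3.244; Φ(1.284) = 90.0%.

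**Applying the protocol's own allowances.**
- Attrition only: 1,015 × 0.75 = 761 per arm; Φ(2.809 − 1.960) = Φ(0.849) = 80.2%.
- Attrition and clustering: 761.25 / 1.15 = 662 per arm; Φ(2.620 − 1.960) = Φ(0.660) = 74.5%.

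**Other readings of the allowances.**

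| Reading | Effective n per arm | Power |
|---|---|---|
| Clustering only, 1,015/1.15 | 883 | 85.7% |
| 25% as ×1.25, no clustering, 1,015/1.25 | 812 | 82.7% |
| 25% attrition, design effect 1.04 (assumed), 761.25/1.04 | 732 | 78.7% |
| 25% as ×1.25, with 15%, 1,015/1.25/1.15 | 706 | 77.2% |

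**Sensitivity to the test formula.** At 1,015, 761 and 662 per arm, the pooled-variance test gives 90.0%, 80.1% and 74.4%. With a continuity correction the values are 89.0%, 78.4% and 72.3%. The choice of formula does not explain the gap.

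**Sensitivity to sidedness.** One-sided, 812 per arm would give 89.5% and 883 would give 91.6%. The article fixes two-sided tests, however, and with both allowances (662) even a one-sided test gives only 83.4%.

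**The 22.25% target (query only).** Half of 12.25 is 6.125, and 28.5 − 6.125 = 22.375. The printed difference, 28.5 − 22.25 = 6.25, is half of 12.5. With 22.375% as the target, power at 1,015, 761 and 662 per arm is 88.8%, 78.5% and 72.7%.

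**The case against.** A reader might infer that the design's true power for this outcome is 75%. The documents do not support so definite a figure, for three reasons.

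- **The clustering loss may be much smaller than 15%.** If 0.04 is an intracluster correlation, a design effect of 1.15 needs 1 + (m − 1) × 0.04 = 1.15, or m = 4.75 participants per household. That is hard to credit for enrolled adults aged 65 and over. With an assumed two per household the design effect is 1.04 and power is 78.7%. Participants are also randomised individually, with minimisation on practice, age and gender rather than household. Members of one household can fall in different arms, so the correlation need not inflate the variance of the treatment contrast as it would under household allocation.
- **Attrition need not mean total loss.** The analysis is by intention to treat. Telephone contacts every 3–4 weeks collect ILI data when a diary has not been completed, and data from before a withdrawal are normally kept. Some participants who stop early may still contribute. As an illustration, an effective loss of only 10% would leave 86.8% power and a loss of 15% would leave 84.9%, both before any clustering.
- **The planned estimates come with 95% confidence intervals.** These show precision directly and limit how far a null result can be over-read.

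These points stand. They widen the plausible range and lower the severity, but they do not restore 90%: if the full 25% is lost, every two-sided reading above falls well short of it.

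A reader might also infer that 22.25% is simply an error. The article never says that it equals 28.5% minus half of 12.25%, and a 50% improvement in efficacy can be read in more than one way. The mismatch is worth a query and no more.

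**Conclusion.** Wrong as written, of moderate severity. The stated 90% is reproduced, at a two-sided 5% level, with all 1,015 enrolled per arm analysed as independent. That conflicts with the same section's account of what the 1,015 contains. The article does not say that the allowances were left out; this is inferred from the close numerical match.

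On the protocol's own figures, power is about 80% after 25% attrition and about 75% if the full 15% clustering allowance also applies, or about 77% if the 25% was a ×1.25 inflation. The chance of missing the assumed effect is then about 20% to 25% rather than 10%. These figures assume that the attrition is a complete loss of data on this outcome and that a two-proportion test approximates the planned model.

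The result should not be stretched to the trial as a whole. Restoring 90% with both allowances would take 1,013.5 × 1.15 / 0.75 ≈ 1,554 per arm, and a reader might infer that enrolment must rise. It need not on this ground: the article justifies enrolment by 85% power for the primary outcome, and that statement is not touched here. About 80% after attrition is also a usual level of power for a secondary outcome.

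**What to change.** In the Sample size section, replace the 90% with power figures that carry their assumptions: for 28.5% versus 22.25% at a two-sided 5% level, about 80% after 25% attrition (761 per arm), and about 75% if the full 15% household allowance is also applied (effective 662 per arm). If the 25% was a ×1.25 inflation, say so and give about 77% for both allowances together. State what the 0.04 is and how it leads to 15%.

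Separately, reconcile 12.25% with 22.25%: confirm how the target was derived, or correct whichever figure is a slip. If 22.375% is adopted, the powers to print are about 78.5% and 73%, not 80% and 75%.

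The cost is a few figures and one or two sentences of text, and a less favourable power statement. Enrolment, endpoints and analysis stay as they are.
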